#### Intervention description {11a}

Participants will be randomised to the intervention or control groups in a 2:1 ratio. In the intervention group, participants will receive an HCV self-test kit delivered in non-identifiable packaging to their home or a preferred mailing address. The kit will include the test itself, instructions for use, additional supporting materials and information on how to access a live chat facility and a call centre in case they have any questions about the test. To evaluate the two sampling methods for HCV self-testing, the first 250 participants in the intervention group will receive an oral fluid-based HCV self-test, and the next 250 participants will receive a blood-based fingerstick HCV self-test. For the oral fluid-based test, participants must swab their upper and lower gums with the test device, place it in the tube provided and read the results within 20 to 40 min of taking the test. For the blood-based test, participants must collect a drop of blood by pricking a finger with a lancet, transfer the blood onto the test device, add the diluent and read the results after 15 min. Participants will be invited to conduct the HCV self-test and then report back if they completed the test as well as enter the test results via the online platform.

In the control group, participants will receive information about the standard of care HCV antibody testing available at local testing sites in their community and information about additional supporting materials, such as access to the live chat facility and the call centre for any questions about testing. At local testing sites, HCV testing involves obtaining blood via a finger prick or obtaining blood from the arm.

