## Statistical methods

### Statistical methods for primary and secondary outcomes {20a}

Data will be analysed using R (version 4.1 or higher). A summary of the statistical analyses that will be completed by the endpoint is shown in Table 2. These analyses will be conducted among the group of participants who received the oral fluid-based HCV self-test with the control group and the group of participants who received the blood-based HCV self-test with the control group.

**Table 2 Tab2:** Statistical analyses to be completed by the endpoint

Endpoint	Statistical analysis methods
1.1 The number and the proportion of participants who report completing the HCV antibody testing in the intervention group 1.2 To assess whether the proportion of participants who report completing the HCV antibody testing in the intervention group is greater than that reported by the participants in the control group by a margin of 20%	Descriptive statistics: Calculation of proportions with 95% CI of the difference in proportions will be evaluated by using the R function prop.test from the “stats” package, which relies on Wilson’s score method. Test of proportions: Two-sided test with a margin of 20%, implemented with the R function “stats::prop.test” with the following hypotheses: *H*_0_: *p*_fo,*I*_ − *p*_fo,*C*_ ≤ 20% *H*_A_: *p*_fo,*I*_ − *p*_fo,*C*_ > 20% where proportions are defined as *p*_*x*,*y*_ [*x* = investigated outcome (fo, pt, ref, trt), *y* = element of {intervention, control}]) comparing the proportion of individuals reporting HCV test results in the intervention versus control groups and between intervention groups. The differences will be reported together with their confidence intervals and the *p*-value related to the statistical comparison mentioned above. The alpha level will be set at 0.025 (2 two-sided tests with an alpha level of 0.05, with the application of Bonferroni correction).
2.1 Number and proportion of HCV antibody-positive individuals made aware of their status in the intervention versus the control group	Descriptive statistics: Statistical testing comparing the numbers of individuals in the intervention versus control groups and between the intervention groups. For details, see the methodology described for endpoint 1.2.
2.2 Number and proportion of HCV antibody-positive individuals who are referred for and complete HCV RNA confirmatory testing in the intervention versus control group	

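### Table 2 gives the oral-versus-blood comparison no hypothesis of its own, only the 20-point self-test-versus-control hypotheses, which cannot show whether uptake differs between kits

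*Protocol article*

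**What the plan says.** All references are to the protocol article.

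- **Hypotheses.** Table 2, endpoint 1.2, introduces them as "Two-sided test with a margin of 20%, implemented with the R function “stats::prop.test” with the following hypotheses". They are H0: pI − pC ≤ 20% and HA: pI − pC > 20%. The group index is defined only as an "element of {intervention, control"}; there is no oral or blood index.
- **Where they apply.** The same sentence continues with "comparing the proportion of individuals reporting HCV test results in the intervention versus control groups and between intervention groups". The difference, its confidence interval and the p-value of that comparison are to be reported.
- **Alpha.** "The alpha level will be set at 0.025 (2 two-sided tests with an alpha level of 0.05, with the application of Bonferroni correction").
- **Lead-in to Table 2.** It names only two comparisons: oral versus control, and "the group of participants who received the blood-based HCV self-test with the control group".
- **Endpoint 2.1.** It plans "Statistical testing comparing the numbers of individuals in the intervention versus control groups and between the intervention groups" and refers to endpoint 1.2 for the method.
- **Why two kits are used.** Intervention description {11a} gives the purpose: "To evaluate the two sampling methods for HCV self-testing". The first 250 intervention participants get the oral kit and the next 250 the blood kit.
- **Source of the 20 points.** Sample size {14} attributes it to expert opinion on self-testing uptake relative to standard care, informed by HIV self-testing.

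**The concern.** A margin of 20 points says how much better self-testing should be than clinic referral. It has no meaning between two kits when neither is the control and neither is expected to win. The natural kit question is whether uptake differs in either direction, so its null is zero. Under the written null, every kit difference up to 20 points counts as no finding. So does every difference in favour of whichever kit happens to be subtracted, and the plan does not say which kit that is.

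A kit p-value will be reported, and its meaning depends on which part of the cell the analyst follows. If the margin is honoured, a non-significant result may be read as the kits performing alike, although the test could hardly have shown otherwise. If the function is honoured, the p-value answers a question that the table does not state.

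**Working it through.** **Inputs.** From the documents: 250 per kit, margin 0.20, alpha 0.025 per test. Assumed: the uptake rates, because the protocol gives none. The plan gives no power figure for the kit comparison, so the only stated figure to reproduce is the alpha: 0.05 / 2 = 0.025. That counts two tests, so the kit comparison has no share of it. A third test at 0.025 would bring the sum to 0.075.

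**Step 1: test the margin as written (upward rejection only).** Z = (d − 0.20) / SE, with SE = √[pa(1−pa)/250 + pb(1−pb)/250]. The cell says two-sided but HA points one way, so both critical values are shown: 1.960 (one-sided 0.025) and 2.241 (two-sided 0.025).

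Example, 80% versus 65%: SE = √(0.16/250 + 0.2275/250) = 0.0394. Z centres on (0.15 − 0.20)/0.0394 = −1.27. P(Z > 1.960) ≈ 1 − Φ(3.23) = 0.06%; exact enumeration of both binomials gives 0.07%.

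**Step 2: test zero difference, two-sided at 0.025.** Pooled SE with the continuity correction 1/250 = 0.004. Same example: pooled rate 0.725, SE0 = √(2 × 0.725 × 0.275/250) = 0.0399. Power ≈ Φ[(0.15 − 0.004 − 2.241 × 0.0399)/0.0394] = Φ(1.44), about 92%; exact 92.6%.

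**Exact results, 250 per kit**

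| True uptake | Margin test, 1.960 | Margin test, 2.241 | Zero-difference test |
|---|---|---|---|
| 85 v 70 | 0.05% | 0.02% | 95.7% |
| 80 v 65 | 0.07% | 0.03% | 92.6% |
| 65 v 50 | 0.12% | 0.04% | 86.3% |
| 80 v 60 | 2.6% | 1.4% | 99.5% |
| 85 v 60 | 26% | 18% | >99.9% |
| 60 v 85 (better kit subtracted) | effectively 0 | effectively 0 | >99.9% |

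With 50–70% uptake in the worse kit, the observed gap must reach about 26–28 points before the margin test is significant at 1.960. Up to a true 20 points, rejection cannot much exceed the nominal level, whatever rates are assumed.

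**Step 3: read two-sided literally, as difference = 20 points tested both ways.** Two identical kits at 80% would then be rejected in over 99.9% of trials, and in about 99% or more at 40–70% uptake. This reading is no more usable.

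**Step 4: run the named function.** A two-group prop.test has no argument for a margin on the difference; it tests equality. Take 150/250 versus 125/250, a 10-point gap:
- prop.test returns p = 0.031, a test of zero difference.
- The written hypotheses give Z = (0.10 − 0.20)/√(0.24/250 + 0.25/250) = −0.10/0.0443 = −2.26, so upward p ≈ 0.99.

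The same data give opposite impressions depending on which half of the cell is followed.

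**Step 5: what a zero-difference test can do at smaller gaps.** Without continuity correction and with reference uptake of 40–70%, its power is about 13–16% at 5 points and 51–64% at 10. The margin test declares a 10-point gap in under 0.002% of trials.

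**The case against.** The strongest reply is that the hypotheses are written only for intervention and control, the lead-in names only kit-versus-control comparisons, and the Bonferroni count is two. On that view the kit comparison has no specified hypothesis rather than a wrong one. This partly stands: no kit order is fixed, so one cannot say that a particular kit is disadvantaged. But the sentence does attach the kit comparison to this test and its p-value, and endpoint 2.1 does so again, so this is more than detail left to an analysis plan.

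A reader might infer that following the plan makes a non-significant kit p-value almost certain. The document does not support that. The named prop.test would return an equality p-value, close to the test recommended here. The low rejection rates arise only if the stated margin is actually tested. What is established is a mismatch between hypothesis and function, and that repairing it by enforcing the margin everywhere would make the kit test uninformative.

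Nor can it be inferred that a programme would be misled into choosing a kit. The confidence interval is already planned and would show the difference and its precision.

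Three further points stand and limit the weight:
- The kit comparison is not among the objectives or outcomes, and the stated power concerns intervention versus control.
- The kits are given in sequence and are not randomised against each other, which Limitations acknowledges, so a corrected test is still confounded with calendar time.
- In the secondary rows the denominators are small. At the general-adult prevalence of 1.9% (an assumption for this population), 250 × 0.019 ≈ 5 antibody-positives per kit, so any test there says little.

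**Conclusion.** The point holds as a fault in the stated hypotheses. The 20-point null is unsuitable for oral versus blood, no reading of it gives a usable kit test, and the function named beside it tests something else. If the margin is enforced, the loss is nearly total at true differences of 15 to 20 points: about 0.02–0.12% and 1.4–2.6% declared, against 86–96% and over 99% for a zero-difference test at the uptake rates shown. Those rates are assumptions, but the cap near the nominal level up to 20 points does not depend on them.

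Severity is minor to moderate. The comparison is peripheral, the interval will be reported anyway, and which p-value would be produced is unsettled. Whether a 20-point null suits the self-test-versus-control comparison is a separate question, not judged here.

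**What to change.** In Table 2:

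1. Limit the 20-point hypotheses to each self-test group versus control.
2. For oral versus blood, define the kit indices and state H0: p_oral − p_blood = 0 against HA: p_oral − p_blood ≠ 0, two-sided.
3. Label this comparison secondary or exploratory and place it outside the two-test Bonferroni count.
4. Make the confidence interval the main result, and state that a non-significant test will not be read as equivalence.
5. State that the kits were allocated in sequence (first 250, next 250), so any kit difference is confounded with calendar time.
6. Use the same zero-difference form for kit comparisons in endpoint 2.1 and the rows that follow its method.

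The cost is a few lines of wording, with no extra data or participants. For the kit comparison, the two-group prop.test then matches its hypothesis. The one small drawback is that the kit p-value no longer comes from the same test as the primary comparison.

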### Trial design {8}

This is a parallel-group non-blinded superiority study comparing HCV self-testing via an online distribution model on the JomTest platform with the standard of care (control). The participant allocation ratio will be 2:1. Participants in the control group will be offered an HCV self-test if they do not go to a primary healthcare clinic for facility-based testing after the completion of two follow-up surveys.

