#### Sample size {14}

The study will enrol a minimum of 750 participants who meet the inclusion criteria. There will be a minimum of 250 participants who receive an oral fluid-based HCV self-test, 250 participants who receive a blood-based HCV self-test and 250 participants in the control group. The study is powered to detect at least a 20% between-group difference in HCV antibody self-testing between the intervention group and the control group, based on 80% statistical power and an alpha level of 0.05. As this study is one of the first to explore the impact of an HCV self-testing distribution model, there are no references available to draw on for the expected difference in between-group uptake of antibody testing rates. The use of a 20% between-group difference in HCV antibody testing uptake is based on expert opinion, according to previous experiences with HIV self-testing and the increases in the uptake of testing seen with the use of HIV self-testing [15].

For the primary objective, the null hypothesis is that there is no significant difference in the proportion of individuals reporting HCV test results in the intervention versus control groups. The alternative hypothesis is that home-based HCV self-testing in the intervention group will significantly increase the proportion of individuals reporting HCV test results.

The study is not powered to detect significant differences in the secondary objectives. However, similarly to the primary objective, the null hypothesis would be no significant difference between the intervention versus control groups, with the alternative hypothesis being that home-based HCV self-testing will result in significantly higher numbers of HCV-infected individuals being diagnosed, linked to care and treated, making it a cost-effective approach to HCV case-finding and elimination.

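### Single-step Bonferroni for the two kit-versus-control tests is valid but gives up some power that Holm's step-down would recover at the same familywise error; an optional improvement

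*Protocol article*

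**What the plan says.** The text above Table 2 (Statistical methods for primary and secondary outcomes {20a}) sets out two comparisons: "the group of participants who received the oral fluid-based HCV self-test with the control group", and the blood-based kit group with the same control group. For endpoint 1.2, Table 2 describes a "Two-sided test with a margin of 20" per cent, with the null that the difference in proportions is at most 20%. It then fixes the multiplicity rule: "The alpha level will be set at 0.025 (2 two-sided tests with an alpha level of 0.05, with the application of Bonferroni correction". No sequential or step-down rule appears anywhere in the article.

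The same cell also mentions comparing proportions "in the intervention versus control groups and between intervention groups", so a between-kit comparison is named but is not among the two tests counted. Table 2 plans 95% confidence intervals for the differences.

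Sample size {14} says the study is "powered to detect at least a 20% between-group difference in HCV antibody self-testing", "based on 80% statistical power and an alpha level of 0.05". It sets a minimum of 250 participants with the oral-fluid kit, "250 participants who receive a blood-based HCV self-test and 250 participants in the control group".

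**The concern.** Under single-step Bonferroni the second kit is held to 0.025 even after the first has been shown superior. Holm's procedure judges the smaller p-value at 0.025 and, if that is rejected, the other at 0.05. It rejects everything Bonferroni rejects and sometimes more, keeps the familywise error at 0.05 under any dependence, and needs no extra data or assumption.

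Intervention description {11a} gives evaluation of the two sampling methods as the reason for using two kits, so a conclusion on each kit is one of the trial's aims. What is at stake is the chance of establishing superiority for a particular kit, or for both. The validity of a positive result is not in question.

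**Working it through.** **The plan's own figure.** 0.05 / 2 = 0.025, exact for two tests. The two-sided critical values are 2.241 at 0.025 and 1.960 at 0.05.

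**Inputs.**
- Groups of 250, 250 and 250, from Sample size {14}. Trial design {8} says "The participant allocation ratio will be 2:1", which is 250 against 250 for each kit if both comparisons use all controls.
- Null: difference at most 20 points (Table 2); or no difference, with a 20-point true difference (Sample size {14}).
- Control testing rate: not given. Assumed 20% to 50%.
- True difference under the margin test: not given. 30 points is taken as an illustration, equal for both kits, with 25 and 35 as variations.

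**Analytic check of one case.** Power of a single test ≈ Φ((d − margin)/SE − z), with SE = √[p_I(1 − p_I)/250 + p_C(1 − p_C)/250]. For p_C = 0.40 and p_I = 0.70:
- SE = √(0.00084 + 0.00096) = 0.0424, and 0.10 / 0.0424 = 2.357.
- At 0.025: Φ(2.357 − 2.241) = 54.6%.
- At 0.05: Φ(2.357 − 1.960) = 65.4%.

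The second figure is an unadjusted 0.05 test, so it is only a ceiling for Holm, approached when the other kit is certain to succeed.

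**Holm against Bonferroni.** Simulation of 1,000,000 trials per scenario: two kit groups, one shared control group, unpooled z statistic, rejections counted in the favourable direction only. Margin 20 points, true difference 30 points in both kits:

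| Control rate | Per kit, Bonferroni | Per kit, Holm | Both kits, Bonferroni | Both kits, Holm | At least one, either method |
|---|---|---|---|---|---|
| 20% | 59.1% | 64.5% | 41.7% | 52.5% | 76.5% |
| 30% | 55.8% | 61.2% | 38.7% | 49.6% | 72.8% |
| 40% | 55.8% | 61.0% | 40.0% | 50.4% | 71.7% |
| 50% | 59.1% | 64.1% | 44.3% | 54.3% | 73.9% |

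The gain is about 5 points per kit and 10-11 points for both kits. The results are internally consistent. The two per-kit powers must sum to P(at least one) + P(both), and P(at least one) is common to both methods, so the per-kit gain is half the both-kit gain. At 40%: (50.4 − 40.0)/2 = 5.2 = 61.0 − 55.8.

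**Other cases, control rate 20-50%.**
- Margin test, true difference 25 points: per kit 15-16% to 17-18%; both kits 5-6% to 9-10%.
- Margin test, true difference 35 points: per kit 91-94% to 94-96%; both kits 85-90% to 90-94%.
- Null of zero, true difference 20 points: per kit 99.0-99.7% to 99.5-99.9%; both kits 98.1-99.4% to 99.1-99.7%.
- As the last, with only 125 concurrent controls per kit (an assumption): per kit 93-97% to 96-98%; both kits 86-94% to 92-97%.

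**Error control.** With both kits exactly at the margin, the chance of any false rejection in the favourable direction was 2.9% under each method; with no margin it was 2.4% under each. The excess over 2.5% comes from the unpooled approximation and affects both alike. With one kit at the margin and the other 30 points above control, the false-rejection rate was 1.4-1.6% for Bonferroni and 2.5-2.7% for Holm, against a nominal 2.5%.

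**Effect of the shared control.** The correlation of the two statistics is the control variance divided by the total. For control 20% and kit 50% it is 0.16/(0.16 + 0.25) = 0.39; for control 50% and kit 80% it is 0.25/(0.25 + 0.16) = 0.61. With Bonferroni power set at 80% per kit, Holm's gain for both kits is 11.1 points at correlation 0, 9.1 at 0.5 and 6.5 at 0.9.

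**The case against.** The plan contains no error here. Bonferroni is valid, simple and conservative, and choosing it is a legitimate preference. That stands, and it is why the point is optional.

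Sample size {14} states only one effect, a 20-point difference. Against zero, Holm adds under 1 point per kit. Against the 20% margin, a true difference of exactly 20 points gives 1.25% power at 0.025 and 2.5% at 0.05, so Holm cannot help. The gain is material only for true differences around 30 points under the margin test, a scenario the protocol does not state. This also stands and limits the claim.

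Holm is not free. Its extra power uses error that Bonferroni leaves unspent when one kit works and the other sits at the margin (2.5-2.7% against 1.4-1.6%), although it stays at about the nominal level. Bonferroni also has simple matching 97.5% intervals and Holm does not. Table 2 plans 95% intervals, however, so the plan does not use that advantage.

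Three stronger readings are tempting but unsupported:
- A reader might infer that the shared control is where Holm gains most. The calculation shows the reverse: positive correlation shrinks the gain.
- A reader might take the gap between power at 0.025 and at 0.05 as Holm's gain. With equal effects it is only a ceiling: 54.6% to 65.4% in the analytic case, against a simulated gain of about 5 points.
- A reader might infer that these tests decide which kit is scaled up. The Strengths section says only that the findings will inform self-testing scale-up in general.

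**Conclusion.** The point holds as a cheap, optional improvement. The protocol fixes a valid rule that is uniformly less powerful than Holm's at the same familywise 0.05. Under Table 2's 20% margin and a true difference of 30 points in both kits, the loss is about 5 points of power per kit and 10-11 points for both kits. There is no loss in the chance of at least one success. For the 20-point difference against zero, the loss is negligible.

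These sizes assume a control rate of 20-50%, equal effects in the two kits, and all 250 controls used in both comparisons. That Holm is never less powerful needs none of these assumptions. Whether the sample size was set for the margin hypothesis at all is a separate and larger question.

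**What to change.** In Table 2, endpoint 1.2, or in the statistical analysis plan, replace the Bonferroni wording for the two kit-versus-control tests with: *Holm's step-down procedure (smaller p-value at 0.025; if rejected, the other at 0.05)*. Date the change before outcome data are examined.

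Two statements should go with it:
- Which confidence interval is reported, because 97.5% intervals no longer match the second decision exactly.
- That the between-kit comparison lies outside this two-test family. If it is confirmatory, write Holm for three tests: 0.05/3 = 0.0167, then 0.05/2 = 0.025, then 0.05.

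The cost is a few words and a less direct link between intervals and decisions. No further participants or data are needed. Keeping Bonferroni would also be defensible.

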As there is currently no quality-assured HCV self-test available, the professional-use OraQuick® HCV Rapid Antibody Test and First Response® HCV Card Test, which have been adapted by the manufacturers for self-testing by being repackaged and labelled with instructions for use, will be used in this study. The OraQuick® HCV Rapid Antibody Test is prequalified by WHO and CE-marked for professional use (sensitivity 98.1%, specificity 99.6%); the First Response® HCV Card Test is CE-marked and currently under WHO review for professional use (sensitivity 100%, specificity 100%). Neither of these professional-use tests are yet registered with the Medical Device Authority in Malaysia. The OraQuick® HCV Self-Test and First Response® HCV Self-Test kits provided to participants in the intervention group will be labelled for Research Use Only (RUO). For these reasons, HCV self-testing results from this study will not be used for clinical decision making, and all participants who report a positive HCV self-test and who report to a clinic will receive follow-up HCV rapid testing in the clinic.

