### Outcomes {12}

The primary outcomes are the number and proportion of participants who report completing HCV antibody testing in the intervention group and to assess whether the proportion of participants who report completing HCV antibody testing in the intervention group is greater than that of the participants in the control group by a margin of 20%.

The secondary outcome measures are as follows: the number and proportion of HCV antibody-positive individuals made aware of their HCV status in the intervention versus the control groups. The number and proportion of HCV antibody-positive individuals who are referred to and complete HCV RNA confirmatory testing in the intervention versus the control groups. The number and proportion of HCV RNA-positive individuals who begin treatment in the intervention versus the control groups. The completion of the Likert scale rankings of ease of use that the participant report regarding the HCV testing process. The cost per test completed and the cost per person diagnosed (serology, RNA) in the intervention versus the control groups.

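### Secondary endpoints 2.1–2.3 are referred to a 20-point margin test that contradicts the protocol's own no-difference null, and their proportions are worded among people known to be positive only through testing

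*Protocol article*

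**What the plan says.** In Table 2 (Statistical methods {20a}), the method for endpoint 2.1 is "Statistical testing comparing the numbers of individuals in the intervention versus control groups and between the intervention groups", followed by "For details, see the methodology described for endpoint 1.2". The cells for 2.2 and 2.3 are empty in the text available and look merged with that of 2.1.

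The endpoint 1.2 method is "Two-sided test with a margin of 20"%, with the null that intervention minus control is at most 20%. The two hypotheses are written for the primary outcome (index fo), but the notation defines the index as "investigated outcome (fo, pt, ref, trt"), so it was drafted to cover further outcomes. The alpha statement is "The alpha level will be set at 0.025 (2 two-sided tests with an alpha level of 0.05, with the application of Bonferroni correction").

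For the secondary objectives, Sample size {14} says that the study is not powered and that the null is no difference between the groups. Its alternative is that "home-based HCV self-testing will result in significantly higher numbers of HCV-infected individuals being diagnosed, linked to care and treated".

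Outcomes {12} defines the first secondary outcome as "the number and proportion of HCV antibody-positive individuals made aware of their HCV status in the intervention versus the control groups". The next two are worded in the same way among antibody-positive and RNA-positive people. The abstract words all three per participant: those who receive a positive result and learn their status, those referred for and completing RNA testing, and those starting treatment.

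**The concern.** There are two separate problems.

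The first is the null. A 20-point margin may suit testing uptake, which can lie anywhere between 0 and 100%. It does not carry over to outcomes that only infected people can reach, and it is not the null that the sample size section sets for them. An analyst who follows Table 2 and one who follows the sample size section would test different hypotheses.

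The second is the denominator. The study collects no specimens, and antibody results come from participants' own reports. The status of anyone who does not test is unknown, so people enter the antibody-positive group by testing and learning the result. Testing is what the intervention is meant to change. A proportion within that group does not compare the arms as randomised, and for 2.1 it is nearly fixed in advance.

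At stake is whether the secondary results can say anything about the stated aim of more people diagnosed, linked to care and treated.

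**Working it through.** The protocol gives no figure for 2.1–2.3 to reproduce. The 750 in Sample size {14} belongs to the primary endpoint and does not decide this point.

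**Inputs.** From the protocol: 250 oral-kit, 250 blood-kit and 250 control participants (Sample size {14}); each kit group compared with control, so 250 vs 250 (Statistical methods {20a}); margin 20 points; alpha 0.025 two-sided per test; prevalence 1.9% in general adults (Background {6a}). The protocol says that estimates for the trial's own groups are limited, so 5% and 10% are added as assumptions. Uptake is also assumed: 40% in control and 60% in a kit group.

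**Step 1. Size of the positive group.** Expected known positives = 250 × prevalence × uptake.

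| Prevalence | Control (40%) | Kit group (60%) | All infected per 250 |
|---|---|---|---|
| 1.9% | 1.9 | 2.85 | 4.75 |
| 5% | 5.0 | 7.5 | 12.5 |
| 10% | 10.0 | 15.0 | 25.0 |

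**Step 2. Endpoint 2.1 among known positives.** Nearly everyone in the denominator is also in the numerator. The proportion is about 100% in both arms, the difference is about 0, and it cannot exceed 20 points.

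**Step 3. Endpoint 2.1 among all randomised.** Take the case most favourable to the trial, with no aware positives in control. Rejecting a difference of at most 20 points needs p − z·√(p(1−p)/250) > 0.20, with z = 2.241 for two-sided 0.025.
- 65/250: p = 0.260, bound = 0.260 − 2.241 × 0.0277 = 0.198. Not met.
- 66/250: p = 0.264, bound = 0.264 − 2.241 × 0.0279 = 0.2015. Met.

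So 26.4% of a kit group would have to be aware positives. At an assumed prevalence of 10%, with every case detected, the chance of 66 or more out of 250 is about 1 in 10^13 (binomial).

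**Step 4. Endpoints 2.2–2.3 among known positives.** Nothing forces these proportions to be equal, so the margin could in principle be met. With an assumed true 90% vs 50% and alpha 0.025, exact enumeration gives the following power (Fisher's test for the zero null; Newcombe lower limit above 20 points for the margin):

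| Positives, kit vs control | Zero null | 20-point margin |
|---|---|---|
| 3 vs 2 | 0% | 0% |
| 5 vs 5 | 2% | 2% |
| 13 vs 13 | 32% | 9% |
| 25 vs 25 | 75% | 21% |

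Once there are enough cases to learn from, the margin removes most of the power. These comparisons remain between groups formed by testing, whichever null is used.

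**Step 5. After the correction.** With a zero null for 2.1, all 250 randomised per group as denominator, and uptake 40% vs 60%, power is about 4%, 6% and 11% at prevalence 1.9%, 5% and 10%. The comparison is then coherent, but still weak.

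**The case against.** **The secondary endpoints are declared unpowered, and the Table 2 cell is headed as descriptive.** This stands as a limit on importance. Yet the same cell plans statistical testing, and a statement about power does not repair a null or a denominator.

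**Carrying the margin over is an inference.** The hypotheses are written only for the primary outcome, and extending the method to 2.2–2.3 assumes a merged cell. That is fair. For 2.1 the cross-reference is explicit, and the notation listing pt, ref and trt supports the extension.

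**The denominator is not settled.** The abstract's per-participant wording is close to what is needed. The accurate criticism is therefore that the protocol words the denominator in two ways, and that the outcomes section and Table 2 use the weaker one.

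Three stronger readings may tempt a reader, and the document does not support them:
- *Raw counts are inflated by 2:1 allocation.* The endpoints are a number and a proportion, the referenced method tests proportions, and the stated comparisons are 250 vs 250. With identical rates, an equal-count test there rejects only 2–4% of the time at nominal 0.05. It would reject 17%, 47% and 80% of the time (at 1.9%, 5% and 10% positives per person) only if the kits were pooled to 500 vs 250. The word numbers is loose, but a bias is not shown.
- *False-positive self-tests count as linkage failures.* The protocol says only that "all participants who report a positive HCV self-test and who report to a clinic will receive follow-up HCV rapid testing in the clinic"; it does not say how a negative re-test is coded. The size also varies. With the oral kit's stated 98.1% sensitivity and 99.6% specificity, the positive predictive value is 0.01864/(0.01864 + 0.00392) = 83% at 1.9% prevalence, but 0.0981/(0.0981 + 0.0036) = 96% at 10%. The blood kit's stated specificity is 100%.
- *No valid answer is possible.* Counts over the 250 randomised per group are a valid comparison, and descriptive results remain usable.

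**Conclusion.** The point holds in two parts. Table 2 refers 2.1, and apparently 2.2–2.3, to a 20-point margin test that contradicts the no-difference null in the sample size section. The outcomes section and Table 2 also take the proportions among people known to be positive only through testing, while the abstract takes them per participant.

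For 2.1 the planned test cannot realistically succeed under either denominator: the difference is about zero among known positives, and about 66/250 against 0 is needed among all randomised. For 2.2–2.3 the margin cuts power (32% to 9% at 13 vs 13 positives), and the comparison is not a randomised one.

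The 66/250 figure rests on the protocol's group sizes, margin and alpha, and on a simple Wald bound. The power figures rest on assumed prevalence, uptake and completion rates. The text is wrong as written and should be corrected before analysis. Importance is moderate: these are secondary endpoints declared unpowered, and the primary conclusion does not depend on them.

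**What to change.** In Table 2, for 2.1–2.3:
- State the null as a difference of zero, in line with Sample size {14}, and drop the 20-point margin. Name a method suited to small counts.
- Use all randomised participants in each compared group as the denominator, in line with the abstract: aware of a positive result, RNA test completed, treatment started. Align Outcomes {12} with this.
- Show the cascade among antibody- and RNA-positive people descriptively only, without a between-arm test.
- Say that proportions, not numbers, are compared.

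This costs rewording and no new data. The proportions will be small, the intervals wide and the power low (about 4–11% for 2.1 per 250 vs 250 comparison under the assumptions above), which the protocol already concedes.
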